### Feasibility/Futility Targets:

| Study Month | 60% of
Accrual
Target | P-value survival | p-value
ALSFRS-R |
|-------------|-----------------------------|------------------|---------------------|
| 3           | NA                          | NA               | NA                  |
| 9           | 141                         | 0.91             | 0.60                |
| 15          | 231                         | 0.82             | 0.37                |
| 21          | 321                         | 0.62             | 0.18                |
| 27          | 360                         | 0.39             | 0.12                |
| 33          | 500                         | 0.24             | 0.12                |
| 39          | 600                         | NA               | NA                  |

For example, on month 15, we require that at least 241 patients have accrued and that the p-value for survival be less than 0.82 or the p-value for ALSFRS-R be less than 0.29. We also we calculate the estimated value of p and it's standard error described above and require that it is significantly better than 67%.

The effect of a 2:1 randomization on power is relatively small. Suppose n is the total sample size of a clinical trial. Then the standard deviation of the test statistic measuring a treatment effect is roughly  $\sqrt{1/(n/2) + 1/(n/2)} = \sqrt{4/n}$  with equal allocation to both treatments. With a 2:1 allocation it is  $\sqrt{1/(2n/3) + 1/(n/3)} = \sqrt{9/2n}$ . Thus the ratio of these is  $\sqrt{8/9}$ . The effective sample size is thus 8/9 of the sample size if we go from a 1:1 randomization to a 2:1 randomization. This only has a small effect of the extent of a difference that we can detect.

### *Analysis of Secondary Outcome Variables*

**Safety and Tolerability.** The safety data will be summarized by treatment group. The treatment groups will be compared with respect to occurrence of each adverse event. Total number of adverse events and abnormal laboratory tests will be compared between groups using Fisher's exact test. Withdrawal, abnormal laboratory tests, vital signs and use of concomitant medications will be assessed to characterize the safety profile of ceftriaxone. Compliance data will be determined for each visit and by treatment group. The time to subject refusal will be compared between treatment groups in order to better determine tolerability. This will be accomplished using a method of survival analysis that allows informative censoring due to death [188]. Descriptive statistics denoting the changes from baseline to the final assessment visit with respect to key laboratory parameters and vital signs will also be provided.

**VC, Dynamometry and Quality of Life.** Our primary analysis strategy is to use a random effects analysis of variance using PROC MIXED in SAS [189]. The basic idea of this model is that each subject has his or her own trajectory with a random, slope, intercept and curvature the average value of which may depend on treatment. Since the subject groups start out the same, the intercept will not depend on treatment but the slope and curvature may. In our trial of topiramate this model was sensitive to a negative effect on muscle strength on treatment.

There was a significant curvature but only the slope was affected by treatment. The advantage of using this model is that it accommodates the variable duration of follow-up that will result from our trial design. We will look carefully at the residuals for this model to be sure that it fits the data. If there appear to be problems with fit, we will use a robust approach of assessing significance where the p-value for any treatment contrast is calculated using a permutation test.

To determine how large an effect on FVC and dynamometry we could detect, we calculated these parameters of this model from the placebo group of our 12-month topiramate study. We did not have dynamometry in that study so we substituted MVIC. Based on the estimates from this study we would have an 80% chance of showing significance at a two-sided  $p=0.05$  level if the true rate of change in the treatment group was a 17% decrease in the rate of decline of the outcome. Interestingly this was the same for all three of the outcomes. The analysis of the extent to which FVC and dynamometry are surrogates for time to death, tracheostomy and PAV will be conducted using the methods of Shah and colleagues [190].

***Analysis of Data on Women and Minorities.*** Our proposal for the analyses of these data follows NIH Guidelines. We intend to use the data from the trial to determine whether women or minorities respond differently to treatment. This will be accomplished by testing for a treatment gender and treatment ethnicity interaction in our efficacy and safety analyses. Although the power of these analyses may be low for the primary outcome the power will be adequate for the secondary outcomes.

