### **6.2.1 Screening and Informed Consent**

At the screening visit, potential subjects will be informed about study procedures and will then sign an informed consent form (Appendix 3). Screening procedures will take place within 28 days of the baseline (randomization) visit. The inclusion/exclusion criteria will be reviewed and a medical history and full physical examination completed. The VC will be determined. Vital signs, weight and concomitant medications will be recorded. Safety laboratory tests will be performed including complete blood count (CBC) with differential, prothrombin time (PT), partial thromboplastin time (PTT), platelets, electrolytes (including phosphorous and calcium), BUN, creatinine, ALT, AST, total bilirubin, albumin, urinalysis including microanalysis (with culture and sensitivity when WBCs are present), and a pregnancy test for women of child-bearing potential. Pregnancy tests will be repeated as necessary throughout the trial.

An abdominal ultrasound will be performed at the screening visit to monitor for biliary disease. Hand held dynamometry for muscle strength will be performed, as well as the ALSFRS-R and Quality of Life questionnaires. The outcome measures performed at this visit will be the pre-treatment measures.

As part of the screening visit, the site investigator will determine the competence of caregiver to administer the study drug at home. Teaching will begin on the method of study drug administration and catheter care. All inclusion and exclusion criteria and safety laboratory tests will be reviewed by the site investigator prior to scheduling the catheter placement visit. If the subject passes all screening procedures and is confirmed as eligible, the catheter placement visit can be scheduled. The site study staff will electronically register the subject to the study and the subject will be assigned a screening identification number. Only registered subjects can go on to have catheter placement and randomization. This process will ensure that only subjects who are eligible for the study will proceed to have placement of a central venous catheter. A log will be kept at the site to record all subjects screened for entry into the study. This information will also be captured electronically. Demographic characteristics of all subjects who are screened will be recorded whether or not they qualify for entry into the study. The reason for non-qualification

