**Study Visits** (Figure 6). After randomization, all subjects will return once a week for the first two weeks, then at week 4. From this point forward, subjects will be seen every 4 weeks until study completion. The visit window is plus or minus 3 days, except for the day 7 visit (+1) for STAGE 1 participants, calculated from the Baseline visit (Day 0). At every study visit participants will be seen for assessment of vital signs, adverse events, and concomitant medications. Urine will be collected and safety laboratory studies will be drawn at screening, weeks 1, 2, 4, and at every study visit following week 4. Study drug accountability and compliance will be assessed at every study visit. The ALSFRS-R will be completed at the screening visit, Week 4 and every 8 weeks starting at week 16. Subjects will have an abdominal ultrasound performed at weeks 4, 8, and 20 to monitor for biliary disease. If there is evidence of biliary disease, the site will repeat the ultrasound as clinically necessary until this condition has resolved. Muscle strength testing, VC, quality of life questionnaires, weight and plasma samples for trough ceftriaxone levels will be obtained every 16 weeks for study duration.

Blood for ceftriaxone levels will be drawn in the morning, prior to first dose. The subjects may receive their first dose at the clinic. This will serve as another opportunity to monitor how the caregiver administers the study drug. At each visit, subjects will be monitored for problems with self-administration of study drug as well as for evidence of drug reaction or skin infections at the central venous catheter site.

**Missed Visits.** When a subject fails to appear for a scheduled visit, the site should contact the subject and a partial evaluation may be performed over the telephone, or if possible by a visit to the subject's home. If a subject is evaluated by telephone, the following information should be

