### **6.2.3 Intervention Discontinuation Evaluations**

In clinical trials in ALS, the primary reasons for stopping intervention early include burden to travel to the site, caregiver burden, disease progression, and adverse events were the reasons. The following are measures to optimize study participation retention:

- Increase the number of sites to reduce the travel burden for study subjects
- Provide reimbursement for subjects to travel to sites for visits.
- Provide reimbursement for study staff to travel to subjects' homes for visits.
- Train site investigators and coordinators to recruit subjects who live within a reasonable distance to the site, and to be willing to travel to the subject if needed.
- Train site investigators at the orientation meeting and quarterly on the adverse event management plan. This is to ensure that all site staff are familiar with the potential adverse events and how to manage them to minimize subject discontinuation from the study.

***Treatment Withdrawals and Loss to Follow-up.*** A subject has the right to refuse study treatment and study visits at any time and for any reason. A subject can also be withdrawn from treatment for intolerable adverse events. All efforts should be made to follow the subject for resolution of the adverse event and for survival. The site investigator must notify the Coordination Center within 24 hours of any subject permanently discontinuing study drug, documenting the reasons for discontinuation in the EDC and on the appropriate source documents.

If a subject discontinues study drug at any time, outcome measures will be performed and documented at the study visits following discontinuation of study drug. Follow-up of subjects who have discontinued study drug will continue in the intention to treat analysis. All attempts will be made to follow these subjects for all outcome measures. These assessments include ALSFRS-R and vital status every 8 weeks. In addition, every effort will be made to encourage subjects to return to the study center every 16 weeks for the full battery of outcome measures. The analysis of data from subjects who stopped treatment and/or refused study visits is discussed in the data analysis section.

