### 9.1.2 STAGE 2 Safety and Tolerability Study

In accordance with the intent-to-treat principle, all subjects randomized will be kept in their originally assigned treatment group for analysis. All randomized subjects will be considered evaluable for tolerability and safety. In the tolerability analyses, subjects will be regarded as a treatment failure if they fail to complete Week 20 of the study on the originally assigned treatment for any reason. The decision will also involve the result of the pharmacokinetic study, since we wish to choose a dosage where the trough levels are greater than  $1\mu\text{M}$ . We consider several possible scenarios, and the decision rules that might be used. The data will be reviewed

by the Steering Committee, using the considerations here as guidelines. Their recommendation would then be reviewed by the DSMB.

We will consider a dosage tolerable if the proportion of treatment failures for a dosage is less than 40% with 80% confidence. With 20 subjects this would occur if 5 or fewer subjects fail to complete the 20-week study. With 20 subjects we will have more than an 80% chance of declaring a dosage tolerable if the true treatment failure rate is 20%. If both dose regimens are tolerable and both achieve 1 $\mu$ M and there are no serious dose related adverse events on the higher dosage and no differences at the one-sided  $p=0.10$  level between adverse event rates that are deemed important then we will use the twice a day dose for the remainder of the study. This would also be the regimen of choice if the one a day regimen did not achieve 1 $\mu$ M and the twice a day regimen was tolerable. Otherwise, we would choose the once a day regimen if it were tolerable and achieved 1 $\mu$ M. If the regimen that achieved 1 $\mu$ M was not tolerable or no regimen achieved 1 $\mu$ M we would consider ending the trial. The decision at this point might involve knowledge of the other pharmacokinetic parameters since if the average dose is high enough it may be worthwhile to continue. In addition we may find that we have equivocal data on the tolerability of whatever regimen achieves 1 $\mu$ M. This would require us to continue the second stage of the study beyond 60 subjects. For instance this might happen if 5-10 subjects in the dosage that achieved 1 $\mu$ M did not tolerate therapy or we had to make substantial changes in the protocol during the first 20 weeks.

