**Treatment Discontinuation Rate Targets:** All analyses will be by “intent to treat”, but the effect of subjects’ discontinuation will be to reduce the power of the study as the treatment effect will be diminished by subjects in the treatment group who don’t continue treatment. This effect will be largest in the survival comparison and will have a minor effect on ALSFRS-R which is only used for the first year to judge efficacy. The hazard ratio used in the power calculation is an “intent to treat” hazard ratio, it reflects the hazard ratio achieved by an effective treatment on all participants combined whether or not they are completely compliant and are treated for the whole period. The “as treated” hazard ratio, the hazard ratio achieved by an effective treatment if all patients are completely compliant, would need to be higher than the “intent to treat” hazard ratio. The relationship of the two hazard ratios does not only depend on the number of subjects that discontinue treatment but on when they discontinue. In the simplest model, described below, it depends on the proportion of time that subjects are treated. If the dropout rate does not meet the treatment discontinuation target that subjects are treated significantly less than 2/3 of the time the recommendation would be to use ALSFRS-R as the primary endpoint and only follow each subject for one year. Survival data would still be collected but would not be expected to be impacted significantly by treatment. The following paragraphs give a justification of this target.

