## 10.4 Adverse Experiences Monitoring and Reporting

An adverse event (AE) is any unfavorable and unintended sign (including a clinically significant abnormal laboratory finding, for example), symptom, or disease temporally associated with a study, use of a drug product or device whether or not considered related to the drug product or device.

The adverse event (AE) definitions and reporting procedures provided in this protocol comply with current CFR 21 Part 312 and device regulations CFR 21 Part 812. The Site Investigator will carefully monitor each subject throughout the study for possible adverse events. All AEs will be documented on eCRFs designed specifically for this purpose. It is also important to report all AEs, especially those that result in permanent discontinuation of the investigational drug being studied, whether serious or non-serious.

For the purposes of this study, symptoms of progression/worsening of ALS, including 'normal' progression, will be recorded as adverse events. The following measures of disease progression will not be recorded as adverse events, even if they worsen (they are being recorded and analyzed separately): vital capacity results, HHD results, grip strength results, and ALSFRS-R ratings.

Subjects will be monitored for adverse events from the time they sign consent until completion of their participation in the study. Relationship of adverse experiences to the experimental intervention will be assessed at each in-person and telephone study visit by recording all voluntary complaints of subjects and by assessment of the clinical features of ALS. Attention will be directed to clinical adverse experiences associated with prior ceftriaxone studies, as well as any evidence of unexpected worsening of the underlying ALS. Laboratory surveillance tests will be obtained as outlined above.

A serious adverse event is defined as an adverse event that meets any of the following criteria:

- Results in death
- Is life threatening: that is, poses an immediate risk of death as the event occurred  
This serious criterion applies if the study subject, in the view of the Site Investigator, is at substantial risk of dying from the AE as it occurs. It does not apply if an AE hypothetically might have caused death if it were more severe.
- Requires inpatient hospitalization or prolongation of existing hospitalization.  

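### The adverse event comparison sets no treatment-emergent window and no exposure adjustment, so pre-dose and off-drug events would be pooled with on-drug events

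*Combined protocol and SAP*

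**What the plan says.** The adverse event analysis is in section 9.1.3, under Analysis of Secondary Outcome Variables (Safety and Tolerability): "The treatment groups will be compared with respect to occurrence of each adverse event". It continues: "Total number of adverse events and abnormal laboratory tests will be compared between groups using Fisher's exact test". It does not say which events qualify by date of onset, and it gives no denominator other than subjects.

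Three other places bear on which events would be counted:

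- **Grouping.** Section 9.1.3, under Treatment Discontinuation Rate Targets, states "All analyses will be by “intent to treat". For Stage 2, section 9.1.2 states "All randomized subjects will be considered evaluable for tolerability and safety".
- **Collection period.** Section 10.4: "Subjects will be monitored for adverse events from the time they sign consent until completion of their participation in the study". Consent comes at screening, and section 6.2.1 says "Screening procedures will take place within 28 days of the baseline (randomization) visit". The schedule in section 6.1 records adverse events at catheter placement and at the pre-randomisation catheter check.
- **Intensity of follow-up.** Under the standard schedule in section 6.2.2, "From this point forward, subjects will be seen every 4 weeks until study completion", with adverse event review and safety laboratory tests. For subjects who have stopped drug, section 6.2.3 says "These assessments include ALSFRS-R and vital status every 8 weeks". Clinic visits every 16 weeks are encouraged but can be declined. Adverse events are not named among these routine contacts.

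**The concern.** A programmer working from this text would have no ground for excluding an event by date. Events before the first dose cannot be caused by the drug, and events well after the last dose mostly reflect background. That background is large here, because section 10.4 counts symptoms of ordinary ALS progression as adverse events. Adding the same background to both arms pulls the comparison towards no difference.

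Section 9.1.3 recognises this mechanism for efficacy and works out how discontinuation shrinks the survival effect. For efficacy the shrinkage is conservative. For harm it works in the drug's favour, and the plan has no matching analysis. Long-term safety and tolerability and adverse event frequency are stated secondary outcomes, so the choice affects a result that will be reported. Left open, it could be settled after the data have been seen.

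**Working it through.** **1. Reproduce the plan's figure.** Section 9.1.3 gives the intent-to-treat hazard ratio as 1/(p/R + (1 − p)), where p is the share of follow-up on treatment and R is the on-treatment ratio, placebo over drug. With p = 0.67 and R = 2: 1/(0.335 + 0.33) = 1.504. With p = 2/3 it is exactly 1.500. The stated 1.5 is confirmed.

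**2. Apply the formula to harm.** A doubling of an event rate on drug is R = 0.5. Inverting to drug over placebo gives p × 2 + (1 − p), which assumes full capture off drug:

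| p | Apparent ratio for a true 2.0 |
|---|---|
| 0.50 | 1.50 |
| 0.67 | 1.67 |
| 0.80 | 1.80 |
| 0.90 | 1.90 |

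**3. Add pre-dose time.** A full 28 days is w = 28/30.44 = 0.92 months at the background rate in both arms. With follow-up of T months, the ratio at p = 0.67 is (1.67T + w)/(T + w). This gives 1.62, 1.64 and 1.65 for T = 12, 18 and 24, so the effect is small unless catheter placement produces many events.

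**4. Move from rates to proportions, since the plan compares occurrence.** With cumulative background hazard m, the risk on placebo is 1 − exp(−m), and on ceftriaxone it is 1 − exp(−1.67m) at p = 0.67 or 1 − exp(−2m) if always on drug.
- m = 0.05: 8.0%/4.9% = 1.64, against 1.95 if always on drug.
- m = 0.30: 39.4%/25.9% = 1.52, against 1.74 if always on drug.

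**5. Vary capture after stopping.** Let a fraction q of off-drug events be recorded, with ceftriaxone on drug for 0.67 of follow-up and placebo for s. The ratio is (1.34 + 0.33q)/(s + (1 − s)q).

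| Placebo on-drug share s | q = 1 | q = 0.5 | q = 0 |
|---|---|---|---|
| 0.67 (equal stopping) | 1.67 | 1.80 | 2.00 |
| 0.80 | 1.67 | 1.67 | 1.68 |
| 1.00 (only ceftriaxone stops) | 1.67 | 1.51 | 1.34 |

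The break-even is s = 1.34/1.67 = 0.80. Sparser capture lowers the ratio below 1.67 only if placebo subjects stay on drug for more than about 80% of follow-up while ceftriaxone subjects stay on for 67%.

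**6. Effect on power.** The arms are about 400 and 200: 540 at 2:1 gives 360 and 180, and Stage 1 adds about 40 and 20. For Fisher's exact test at two-sided 0.05, with background risks that are assumptions:
- 5% placebo risk: 55% power for a risk ratio of 2, and 30% for 1.67.
- 10% placebo risk: 89% and 60%.

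An on-treatment rate would recover the ratio of 2 under the step 2 assumptions. It would not recover all of the power, because it uses less follow-up.

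**The case against.** The case on the other side has real force, and several stronger readings fail against it.

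- **A reader might infer that the plan states a consent-to-end comparison.** It does not. The safety paragraph names no window. The intent-to-treat sentence sits in a passage about power for survival and ALSFRS-R, and section 10.4 is a collection rule. The all-follow-up comparison follows from these texts plus silence.
- **A reader might take 1.67 as the expected dilution.** The 67% is the minimum on-treatment share for keeping survival as a primary endpoint. It is not a forecast and was not set for safety.
- **A reader might apply the dilution to every harm.** Section 2.2.2 describes neutropenia and interstitial nephritis that typically appear within weeks. Such early events are counted before most stopping can occur. Events that trigger suspension under section 8.1, such as symptomatic biliary sludge, precede the stop by definition. The formula does not describe either kind, and averaging an early hazard over long exposure would itself blunt it.
- **A reader might infer that sparser follow-up hides harm.** With equal stopping it moves the ratio back towards 2, as step 5 shows. The documents give no on-drug share by arm, so they do not support a claim that a harm signal would vanish or reverse. Capture off drug may also be better than section 6.2.3 suggests. Section 10.4 has adverse events assessed at in-person and telephone visits, and section 6.2.3 asks that events be followed to resolution.

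The plan also compares time to refusal by arm, assesses withdrawals and has the DSMB review safety about every six months. These help with tolerability and oversight. None of them supplies an on-drug or exposure-adjusted comparison of adverse events, so the gap remains.

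**Conclusion.** The concern holds as a gap in specification with a bounded effect. No treatment-emergent window or exposure adjustment is defined, and the comparison as written would mix pre-dose, on-drug and late off-drug events. For a sustained on-drug excess the attenuation of a true doubling is moderate: to 1.67 at the 67% floor, and to 1.80-1.90 at 80-90% exposure. This rests on a constant excess rate while on drug, no carry-over after stopping, full capture off drug, and events rare enough for rates and risks to agree. Early and stop-triggering events are largely unaffected. Any further loss from sparser capture would need clearly more loss of on-drug time on ceftriaxone than on placebo, which the documents do not establish.

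**What to change.** In section 9.1.3, under Safety and Tolerability:

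1. Define treatment-emergent adverse events as those with onset from the first dose to the last dose plus a lag fixed in advance. The 30-day telephone call in section 6.2.4 should not supply the lag by default, because it follows the final study visit and not an early discontinuation. Say how temporary suspensions and drug holidays count.
2. Report these events by arm as exposure-adjusted rates or as time to first event. Time to first event suits early harms better. Proportions restricted to on-drug time are not enough: if only the ceftriaxone arm stops, at 67% exposure and m = 0.05, the ratio of proportions is (1 − exp(−1.34 × 0.05))/(1 − exp(−0.05)) = 1.33 for a true doubling.
3. List pre-dose events and later off-drug events separately.
4. Present the all-follow-up comparison by randomised arm alongside, with neither replacing the other.

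A sentence in section 6.2.3 saying whether adverse events are asked about at the 8-week contacts would also settle the capture assumption.

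The cost is analysis-plan wording and one derived variable. Event start dates (10.4.1), syringe counts and diaries (5.2.3) and discontinuation records (6.2.3) are already collected. The downside is that on-drug time is not a fully randomised comparison and can be distorted by informative stopping, which is why both analyses are kept.
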